### Randomization

Parents are randomly assigned to either the CBT-based or PEP-based PAC intervention group following their completion of pre-intervention assessments, but before the initiation of the PAC sessions. Given that parents and their children are recruited and enrolled into the group-based interventions in several cohorts, we use a computer-generated, block randomization approach, which is completed by one of our research team members who has no direct contact with participants. Parents will be blinded to group assignment, and while they are aware that there are two groups of parents receiving the PAC intervention, they are unaware of the modality and methodological differences between CBT and PEP.

### Statistical analysis

Data cleaning, analyses, figures, tables, and statistical sections for dissemination are conducted by a blinded biostatistician with the Biostatistics Consulting Group within the Women and Children’s Health Research Institute (http://www.wchri.org) at the University of Alberta. Spotfire S + 8.2 (TIBCO Software Inc, 2010) and SAS 9.3 (SAS Institute Inc, 2010) will be used for analyses. Analyses are conducted both with PAC intervention completers only and with all participants (to evaluate effectiveness). Continuous variables are described by summaries (e.g., means, medians, ranges and SDs) and frequency distributions are determined for categorical variables. For the primary and secondary outcome variables, the percent change from pre- to post-intervention (as well as 6- and 12-months follow-up) for both groups is determined and summarized along with the 95% confidence intervals (CIs) for mean percent change. Boxplots and histograms are used to display the percent change for these variables; bar charts are used for categorical variables. Our analyses are conducted separately for each mean percent change at each observation time (i.e., pre-intervention to post-intervention, pre-intervention to 6-month follow-up, and pre-intervention to 12-month follow-up). Statistical tests are set at conventional levels (p < 0.05) and all analyses are intention-to-treat. Multiple imputation methods may be used in the event of missing data. To minimize the risk of bias, a research team member with no direct contact with enrolled families is leading the data analyses.

To compare interventions, one-sided independent samples Student’s t-test assesses percent changes in BMI z-score (primary objective); if required, data transformations are used to ensure data normality. A similar process is used to determine intervention-mediated changes in other physiological, behavioural, and psychosocial outcomes (secondary objectives). In addition, the percentage of families with improved categorical outcomes (i.e., those who do/do not meet recommendations from *Eating Healthy with Canada’s Food Guide*) is compared across interventions using a one-sided independent samples proportion tests. A multivariable linear regression model is developed for the primary outcome (percent change in BMI z-score) to determine the intervention group effect while controlling for potential confounders (i.e., cohort, percent attendance, household income). If any of the intervention groups include siblings, CIs are adjusted using variance inflation factors, and univariable or multivariable random intercept mixed effects models are used in lieu of Student’s t-tests and multivariable linear regression, respectively. Analogous calculations are made to compare the percent change from pre-intervention to 12-month follow-up, although intervention attrition may reduce our power to detect a significant difference. Mixed effect models are developed to examine the effects of the interventions on primary and secondary outcomes over time. This approach allows all pre-intervention, post-intervention, and follow-up data to be included in our modeling. For all models, residual diagnostics are used to assess model assumptions and appropriate transformations and/or non-linear terms are included as necessary. Our reporting of study results is in accordance with the CONSORT statement [91].

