### The PAC intervention: similarities and differences between CBT and PEP versions

Both intervention arms in the trial are the same in frequency of contact (16 sessions), content (identical information is delivered), mode (group format), duration (60 – 90 minutes per session), intervention goals (related to nutrition and physical activity), and the number of group leaders (two per group). Importantly, the intervention arms differ in how information is conveyed to parents, and how parents work towards attempting, achieving, and maintaining healthy cognitive and behavioural changes. All families are encouraged to manually monitor their daily nutrition, moderate-to-vigorous-physical activity (MVPA), sleep and leisure-time screen time (LTST) throughout the intervention period, and tracking tools are available for all family members (parents, children, other family members). To encourage monitoring, small prizes (e.g., cookbooks, activity-promoting toys and games) are awarded at three points during the 16-session intervention period (e.g., on week 6 for tracking completed in weeks 1 – 5, on week 11 for tracking completed in weeks 6 – 10, and on week 16 for tracking completed in weeks 11 – 15). Families are eligible to receive prizes in each of the three time periods regardless of their consistency with monitoring in previous time frames. For both CBT and PEP, families strive to achieve the same lifestyle goals (please see Table 2), which are based on evidence-based recommendations [55-57].

**Table 2 T2:** Lifestyle goals for the CBT and PEP Versions of the PAC intervention

	
**1. Diet**	Daily vegetable and fruit intake: ≥5 servings
	Daily grain product intake: ≥50% servings as whole grains
	Daily sugar-sweetened beverage intake: 0 servings
**2. Physical Activity**	Daily steps: ≥12,000 (girls); ≥15,000 (boys)
	Daily moderate-to-vigorous physical activity: ≥90 minutes
**3. Sedentary Activity**	Daily leisure time screen time: ≤90 minutes

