### Outcome measures

Child BMI z-score is the primary outcome for this study. Several investigations [68-72] have included BMI z-score as the primary outcome in pediatric weight management studies since it represents a clinically-meaningful indicator of weight status in childhood. Beneficial changes in this variable are linked to improvements in obesity-related risk factors for chronic diseases including insulin resistance, dyslipidemia and high blood pressure [73,74]. The inclusion of this outcome is also informative when comparing effect sizes across studies.

Consistent with recommendations for evaluating the effects of pediatric obesity treatment [12,17], we are measuring a number of secondary physiological, behavioural, and psychosocial variables in families. Along with assessing nutrition and physical activity behaviours, anthropometry, and cardiometabolic risk factors, we are testing potential moderating (e.g., sex, age) and mediating (e.g., parents’ lifestyle behaviors) variables to explore how different child and parent features interact with and respond to the different interventions and hypothesize how they contribute to changes in child health outcomes [75]. This is a valuable, but often overlooked process that provides a better understanding of the mechanisms of lifestyle change. This approach, in turn, allows our team to improve our interventions since we can distinguish between effective and ineffective intervention components [76].

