### Sample size

We are enrolling 90 families (n = 45 families × 2 PAC intervention arms) in this study. Based on our clinical experience, we anticipate a 33% level of attrition, which should yield post-intervention data on 60 families. With a total sample size of 60 families (n = 30 per arm), we are able to detect a minimum difference of 0.5 in BMI z-score change between the CBT and PEP intervention groups. To our knowledge, no experimental work has been done to define specific weight-related goals for pediatric obesity interventions. However, our 0.5 BMI z-score difference is based on a review by Epstein and colleagues that suggested a reduction of this magnitude is clinically meaningful [89]. Sample size calculations were completed using *PASS 2008* (http://www.ncss.com), and assumed a standard deviation (SD) of 0.83 for each group, a one-sided significance level of 0.05, and a desired power of 80%. This SD was based on preliminary findings that included pre- and post-intervention BMI z-score data [90]. Multiple linear regressions are able to detect an R^2^ value of 10% for the effect of intervention on percent change in BMI z-score at a 0.05 significance level with 80% power, assuming that the inclusion of five control variables explains 20% of the variability in change in BMI z-score.

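### The primary analysis uses percent change in BMI z-score, while the trial is sized on an absolute 0.5 z-score difference, so the primary estimate cannot be read against its own target

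*Protocol article*

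**What the plan says.** All references are to the protocol article.

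- **Outcome measures** names the variable but not the scale of change: "Child BMI z-score is the primary outcome for this study".
- **Sample size** works in absolute z-score units. With 30 families per arm, "we are able to detect a minimum difference of 0.5 in BMI z-score change between the CBT and PEP intervention groups". The calculation "assumed a standard deviation (SD) of 0.83 for each group", with one-sided alpha 0.05 and 80% power. The section also says where the target comes from ("our 0.5 BMI z-score difference is based on a review") and that a reduction of this size is clinically meaningful.
- **Sample size** also has a second power statement, for multiple regression: an R² of 10% for the intervention effect on percent change in BMI z-score, with five control variables explaining 20% of the variability in change.
- **Statistical analysis** moves to the percent scale. The summaries and 95% confidence intervals are defined by "For the primary and secondary outcome variables, the percent change from pre- to post-intervention" and the same quantity at the follow-up visits. For the primary objective, "t-test assesses percent changes in BMI z-score (primary objective"). The multivariable regression also takes percent change as the primary outcome. The covariates it names are cohort, attendance and household income; baseline BMI z-score is not among them.
- **Statistical analysis** applies a similar process to the secondary outcomes. It also plans mixed effects models over time, without saying which scale they use.

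**The concern.** The effect that justifies the trial and the effect that will be tested are different quantities. The first is a difference in z-score units. The second is a difference in the ratio of change to baseline. The article gives no conversion between them and no target or SD for the t-test on the percent scale.

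A BMI z-score is already standardised, and its zero is the reference median. Dividing the change by baseline weights equal absolute changes by 1/baseline, so a child closer to the reference median counts for more than a heavier child with the same z-score loss. The mean percent difference then depends on the mix of baseline z-scores as well as on the treatment effect. At stake is whether the primary result can be held against the 0.5 criterion. Two scales in one plan also leave room to choose between them once results are known.

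The percent rule reaches the secondary outcomes too. For a variable that can be zero at baseline, such as recorded minutes of moderate-to-vigorous activity or a symptom score, percent change is undefined.

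**Working it through.** **1. The plan's own sizing, on the absolute scale.** Inputs from Sample size: difference 0.5, SD 0.83, one-sided alpha 0.05, power 80%.

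n per arm = 2 × (1.645 + 0.842)² × 0.83² / 0.5² ≈ 34.1, so 35, against the stated 30. At 30 per arm the power is 75.4% (normal approximation) or 74.6% (t distribution). The difference detectable at 80% power is 0.53 to 0.54, which matches the plan only if rounded to 0.5. The attrition step reproduces: 60 / (1 − 0.33) = 89.6, so 90. The shortfall at 30 per arm is a separate matter, and nothing below depends on it. What matters here is that every input is in z-score units.

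**2. The regression power statement.** f² = 0.10 / (1 − 0.20 − 0.10) = 0.143. With N = 60, the noncentrality is 60 × 0.143 = 8.57 on 1 and 53 degrees of freedom, and power is 82.0%. This reproduces the stated 80%. An R² is a share of variance, however. Turning it into a percent difference needs the SD of percent change, and turning that into z-score units needs the baseline distribution. The article gives neither.

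**3. What 0.5 means as a percent of baseline.** Percent = 100 × 0.5 / baseline z. Percentiles are converted with the standard normal distribution.

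| Baseline z | Where it lies | 0.5 as percent of baseline |
|---|---|---|
| 1.04 | 85th percentile, the entry limit (Recruitment) | 48.1% |
| 2.00 | illustrative | 25.0% |
| 2.33 | 99th percentile (Strengths and limitations) | 21.5% |
| 3.00 | illustrative | 16.7% |

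Strengths and limitations expects almost all children to be severely obese, so the last two rows matter most. Between them the ratio is 21.5 / 16.7 = 1.3. Conversely, a 20% fall is 0.20 × 2.33 = 0.47 units at one end and 0.20 × 3.0 = 0.60 at the other. Even within this range, one percent figure falls on both sides of 0.5.

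**4. One true effect under different baseline mixes.** The article gives no baseline distribution, so these are assumptions. With a constant effect of 0.5, the expected percent difference is 100 × 0.5 × E(1/baseline). For a uniform baseline from a to b, E(1/baseline) = ln(b/a) / (b − a).

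- Uniform 1.04 to 3.0: ln(2.885) / 1.96 = 0.540, giving about −27%.
- Uniform 2.33 to 3.0: ln(1.288) / 0.67 = 0.377, giving about −19%.

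**5. Power on each scale.** Simulation of 20,000 trials, 30 per arm, change SD 0.83, constant true difference 0.5, one-sided t-test at 0.05:

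| Assumed baseline | Power, absolute | Power, percent | Mean percent difference | SD of percent change |
|---|---|---|---|---|
| Uniform 1.04–3.0 | 74.3% | 70.8% | −26.9 | 47.0 |
| Uniform 1.04–2.5 | 74.3% | 72.0% | −30.0 | 51.6 |
| Normal, mean 2.0, SD 0.5, truncated to 1.04–4 | 74.1% | 71.9% | −26.0 | 44.4 |
| Normal, mean 2.3, SD 0.4, truncated to 1.04–4 | 75.1% | 73.5% | −22.5 | 37.9 |
| Uniform 2.33–3.0 | 74.8% | 74.6% | −18.9 | 31.4 |

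The power loss runs from about 0 to 4 points. The SD on the percent scale runs from 31 to 52 points, so 0.83 has no single counterpart there.

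**The case against.** The strongest case on the other side has four parts.

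- **The ratio is defined for every child.** Entry at or above the 85th percentile keeps every entry z-score at about 1.04 or more, so percent change always exists and can be read as the share of the excess over the reference median that is lost. This stands: the measure is a poor match to the target, but it is not meaningless. If the true effect were proportional to baseline, percent change would be the natural scale. The article does not say that it is, and its target is absolute.
- **The practical effect is small in this population.** This also stands. In the expected range 0.5 corresponds to about 17% to 21%, and the simulated power loss is near 0.
- **Some of the power work is on percent change.** The regression statement is, and it reproduces. It qualifies the mismatch but does not resolve it, because an R² of 10% cannot be set against 0.5.
- **The mixed models may supply an absolute estimate.** They include pre-intervention values as data, which suggests z-score units. They are not the primary test, and their scale is not stated.

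A reader might infer more about the secondary outcomes, for instance from the Table 2 goal "Daily sugar-sweetened beverage intake: 0 servings": that children already at goal are excluded by arithmetic. The document does not support this. Drink servings are a lifestyle goal and are not among the measures listed under Dietary intake. For moderate-to-vigorous activity the goal is at least 90 minutes, so a zero baseline is furthest from goal. Nothing says that children with a zero baseline are dropped, and their handling may be set out in an analysis plan that is not shown.

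**Conclusion.** The mismatch holds. Sample size fixes the target and SD in absolute z-score units, Statistical analysis fixes the primary test, regression and intervals on percent change, and nothing connects the two. The planned primary estimate cannot be judged against the 0.5 criterion without the baseline distribution.

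The cost is mainly interpretability. A reader might infer that percent change biases the comparison or badly weakens the trial, and neither follows. Randomisation balances baseline in expectation, so with no treatment effect neither arm is favoured. The power loss is about 0 to 4 points under the assumed baselines with a constant absolute effect. A reader might also infer a nearly threefold spread in what 0.5 means (48% against 17%). That needs children at the entry limit, and the article suggests few will be there.

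For secondary outcomes the point is narrower: percent change is undefined for any variable with a zero baseline. How many children this affects cannot be known from the document. The correction is needed because it concerns the primary variable and the only stated criterion for a meaningful effect.

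**What to change.** State one primary variable in z-score units: the post-intervention BMI z-score, or the absolute change from baseline, adjusted for baseline BMI z-score. Use it in the primary comparison, the multivariable regression and the 95% confidence intervals, and add baseline BMI z-score to the named covariates. Keep percent change as a descriptive or supportive summary. State the scale of the mixed models in the same place.

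Analyse continuous secondary outcomes in their measured units, adjusted for baseline. Report percent change only descriptively, and only where the baseline cannot be zero.

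If percent change is to remain primary, the plan needs a justified target and SD on that scale and a sample size derived from them. The article contains none of these.

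The recommended change is to wording only. Baseline and follow-up z-scores are already collected, so no new data are needed. It should be made before outcomes are compared by arm.

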**Methods/Design:**

This study is a pragmatic, two-armed, parallel, single-blinded, superiority, randomized clinical trial. The primary objective is to examine the differential effects of a CBT-based PAC *vs* PEP-based PAC intervention on children’s BMI z-score (primary outcome). Secondary objectives are to assess intervention-mediated changes in cardiometabolic, lifestyle, and psychosocial variables in children and parents. Both interventions are similar in frequency of contact, session duration, group facilitation, lifestyle behaviour goals, and educational content. However, the interventions differ insofar as the CBT-based intervention incorporates theory-based concepts to help parents link their thoughts, feelings, and behaviours; these cognitive activities are enabled by group leaders who possess formal training in CBT. Mothers and fathers of children (8–12 years of age; BMI ≥85^th^ percentile) are eligible to participate if they are proficient in English (written and spoken) and agree for at least one parent to attend group-based sessions on a weekly basis. Anthropometry, cardiometabolic risk factors, lifestyle behaviours, and psychosocial health of children and parents are assessed at pre-intervention, post-intervention, 6-, and 12-months follow-up.

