### Timeframe

Data are collected from families at pre-intervention, post-intervention, 6-, and 12-months follow-up. For practical reasons, at each time point, data collection occurs within a 2-month window (e.g., within 8 weeks before the first PAC session, within 8 weeks after the last PAC session, and between 4 weeks before to 4 weeks after each of the 6- and 12-month follow-up time points). Clinical and research experience by our team [48] revealed that this timeframe is needed to accommodate families’ schedules and clinical capacity to complete data collection, which also differentiates our real-world, comparative effectiveness research [51] from more stringent criteria that are applied in the context of efficacy studies. Data collection is completed by clinicians working within the PCWH, and given the real-world, applied health services environment within which the study is conducted, we are unable to blind them from knowing which families are receiving the CBT- and PEP-based versions of the PAC intervention [52].

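### The comparison of improved categorical outcomes leaves unclear whether status or change is meant, and its test uses no baseline status although that is measured

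*Protocol article*

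**What the plan says.** In the protocol article, Statistical analysis, one sentence covers the categorical outcomes. It takes "the percentage of families with improved categorical outcomes (i.e., those who do/do not meet recommendations from" the food guide), and this percentage "is compared across interventions using a one-sided independent samples proportion tests". The sentence names no baseline state, denominator or covariate.

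Other parts that bear on it:

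- Timeframe: "Data are collected from families at pre-intervention, post-intervention, 6-, and 12-months follow-up". The Dietary intake section converts the food records to food-guide servings. The Randomization section places allocation after the pre-intervention assessments. Baseline status is therefore known for randomised families and cannot be affected by allocation.
- Outcome measures: "Child BMI z-score is the primary outcome for this study". The categorical dietary outcomes are secondary.
- Statistical analysis, later in the same paragraph: "Mixed effect models are developed to examine the effects of the interventions on primary and secondary outcomes over time", followed by "This approach allows all pre-intervention, post-intervention, and follow-up data to be included in our modeling".
- The same section brings in random-intercept models if siblings are enrolled. It states them as replacements for the t-tests and the linear regression only.

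**The concern.** Improvement is a change from an earlier state. Meeting or not meeting a recommendation is a state at one time. The sentence joins the two and does not say which is counted. If status is counted, a family that met the recommendation at pre-intervention and still meets it appears in the percentage improved, and the label misdescribes the figure. If change is counted, the sentence does not say whether families already meeting the goal stay in the denominator, or how families that lapse are treated.

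The second matter is precision. Whether a family met a recommendation beforehand is likely to predict whether it meets it later. The trial collects that information, yet the named test does not use it. With about 30 families per arm at post-intervention, precision is scarce.

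**Working it through.** **The plan's own figures.** The documents give no prevalence, effect size or power for any categorical outcome, so there is no figure to reproduce. The only usable input is the number of families. Sample size states: "We are enrolling 90 families (n = 45 families × 2 PAC intervention arms) in this study". With the 33% attrition given there, 90 × (1 − 0.33) = 60.3, so about 60 families, or 30 per arm.

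**Does the definition matter?** Take an assumed case in which 40% meet at baseline. Retention among them is 70% (PEP) and 90% (CBT). Among the rest, 30% (PEP) and 60% (CBT) newly meet.

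- Meeting at follow-up: PEP 0.4 × 0.70 + 0.6 × 0.30 = 46%; CBT 0.4 × 0.90 + 0.6 × 0.60 = 72%. The difference is 26 points.
- Newly meeting, all families in the denominator: PEP 0.6 × 0.30 = 18%; CBT 0.6 × 0.60 = 36%. The difference is 18 points.

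Simulated one-sided power at 30 per arm is 65% for status, 48% for newly meeting and 71% for status stratified by baseline. Two analysts who read the sentence differently would report different results from the same data.

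**How many families counted as improved would already have met the goal, if status is counted?** Let b be the share meeting at baseline. Let 25% of PEP non-meeters meet at follow-up (odds 1/3), and let p1 be the PEP rate among baseline meeters. For a baseline odds ratio of 5, 10 or 20, the odds are 5/3, 10/3 or 20/3, so p1 = 0.625, 0.769 or 0.870. The share is b·p1 / (b·p1 + (1 − b)·0.25).

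- b = 5%: 12% to 16%
- b = 10%: 22% to 28%
- b = 30%: 52% to 60%
- b = 50%: 71% to 78%

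For example, b = 30% and odds ratio 5 give 0.1875 / (0.1875 + 0.175) = 52%.

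**Precision.** Under the same model with a treatment odds ratio of 4, 57% of CBT non-meeters meet at follow-up (odds 4/3). I simulated 100,000 trials per setting at 30 per arm and one-sided 5%. The comparison is the pooled two-proportion z-test against a Mantel-Haenszel test stratified by baseline status.

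| Meeting at baseline | Baseline OR | Planned test | Stratified test | Gain (points) |
|---|---|---|---|---|
| 5% | 5 | 80.2% | 81.8% | 1.6 |
| 5% | 10 | 79.2% | 81.5% | 2.3 |
| 5% | 20 | 78.5% | 81.4% | 2.9 |
| 10% | 5 | 79.2% | 81.3% | 2.1 |
| 10% | 10 | 77.1% | 80.7% | 3.6 |
| 10% | 20 | 75.0% | 79.7% | 4.7 |
| 30% | 5 | 74.8% | 79.3% | 4.5 |
| 30% | 10 | 68.2% | 76.3% | 8.1 |
| 30% | 20 | 62.1% | 73.4% | 11.3 |
| 50% | 5 | 71.6% | 77.5% | 5.9 |
| 50% | 10 | 60.6% | 71.2% | 10.6 |
| 50% | 20 | 51.9% | 65.5% | 13.6 |

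With no treatment effect, the planned test rejects in 4.5% to 5.2% of trials and the stratified test in 4.9% to 5.1%. Both hold the nominal level.

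**Would analysing only baseline non-meeters do as well?** Not reliably. At a baseline odds ratio of 5, its power is 70% against 75% for the planned test when 30% meet at baseline, and 58% against 72% when 50% do.

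**The case against.** A reader might infer that the plan miscounts improvers. The text does not establish that. The parenthesis lists both those who do and those who do not meet the recommendation. Taken as a definition of improved, it would make families who fail the recommendation improved as well. It may simply name the two categories, with improvement meaning a move between them. The surrounding text is about change from pre-intervention, which favours that reading. On it, nobody already meeting the goal is counted and baseline does enter the outcome. This objection stands: the defect is ambiguity, not a shown miscount.

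A reader might also infer that ignoring baseline biases the comparison. It does not. Allocation is random, the null rejection rates above are near 5%, and chance baseline imbalance is already covered by that error rate.

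The plan also has mixed effect models that use pre-intervention data for the secondary outcomes. That deserves weight, but the section does not say that they cover binary outcomes, and its other modelling language (linear regression, residual diagnostics, transformations) suits continuous data. The proportion test is the only one named for these outcomes.

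Finally, a protocol article may leave operational definitions to a fuller document. That excuses missing detail. It does not excuse a label and gloss that disagree in the text that is present. The size of the gain does depend on rates that the documents do not give, and it is small if few families meet the goal at baseline.

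**Conclusion.** The point holds as a matter of clarity and efficiency. The outcome's wording can be read as status or as change, and the named test has no baseline term although baseline status is measured before randomisation. The test is valid; it is less precise than one that uses the baseline. The gain from stratifying is about 2 to 5 points of power if 5% to 10% of families meet the recommendation at baseline, and about 4 to 14 points if 30% to 50% do. These figures rest on assumptions: 30 per arm, 25% of PEP non-meeters meeting at follow-up, a treatment odds ratio of 4 and a baseline odds ratio of 5 to 20. The primary outcome is untouched. Importance is minor.

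**What to change.** Rewrite the sentence along these lines: the categorical outcome is meeting the recommendation at post-intervention, 6 months and 12 months; arms are compared by a Mantel-Haenszel test or a logistic regression adjusted for whether the recommendation was met at pre-intervention; the adjusted risk difference is reported with its 95% CI. If few families meet the goal at baseline (5% of 60 is 3 families), the Mantel-Haenszel form is the safer choice, because a logistic fit can become unstable in so small a stratum.

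Drop the word improved for this outcome. Do not restrict the analysis to families not meeting the goal at baseline, since that can lose power.

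State how siblings are handled in this analysis, because the random-intercept models are given only in place of the t-tests and linear regression. Say also whether the mixed effect models over time include the binary outcomes.

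The cost is a few sentences of analysis text. It needs no new data, visits or families.

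### The primary t-test on percent change in BMI z-score uses neither baseline BMI z-score nor cohort, which gives up precision (not validity) that the trial could have at almost no cost

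*Protocol article*

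**What the plan says.** All references are to the Protocol article.

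- **Primary test** (Statistical analysis): "one-sided independent samples Student’s t-test assesses percent changes in BMI z-score (primary objective". No covariate is attached to it.
- **Supporting regression** (same section): "A multivariable linear regression model is developed for the primary outcome (percent change in BMI z-score", with the arm effect estimated while "controlling for potential confounders (i.e., cohort, percent attendance, household income" are held constant. Baseline BMI z-score is not named.
- **Other models** (same section): random-intercept models replace the t-test and regression only when siblings are present ("If any of the intervention groups include siblings, CIs are adjusted using variance inflation factors"). Separate mixed models over time are also planned: "This approach allows all pre-intervention, post-intervention, and follow-up data to be included in our modeling". Neither is the stated primary test.
- **Randomization**: parents are allocated "following their completion of pre-intervention assessments, but before the initiation of the PAC sessions", so each child's baseline is known before allocation. Families are "enrolled into the group-based interventions in several cohorts, we use a computer-generated, block randomization approach". Stratification by cohort is not stated.
- **Sample size**: 30 evaluable families per arm, a difference of 0.5 in BMI z-score change, SD 0.83, one-sided 0.05 and 80% power. For the regression, five control variables are assumed to explain 20% of the variability in change.

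**The concern.** Baseline BMI z-score is normally a strong predictor of the follow-up value. Here it is collected before allocation in every randomised family, so it is a legitimate covariate that costs nothing to obtain. The primary test leaves it out. Expressing change as a percentage brings baseline in as a divisor, which is not adjustment: it makes a child's contribution depend on where that child started. Cohort, the unit in which families enrol and the stated reason for blocking, is also absent from the primary test.

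With about 30 children per arm, the stake is a wider confidence interval and a lower chance of detecting a real difference. The protocol's own regression assumption credits covariates with explaining a fifth of the variability, but the test of the primary objective uses none of them.

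**Working it through.** **1. The protocol's own figures.** Inputs from Sample size: difference 0.5, SD 0.83, 30 per arm, one-sided 0.05.

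- Standard error = 0.83 × √(2/30) = 0.214. Noncentrality = 0.5/0.214 = 2.33.
- Power = 74.6% by the exact t calculation and 75.4% by the normal approximation, against the stated 80%. Reaching 80% takes 35 per arm.
- The regression figure does reproduce. With f² = 0.10/(1 − 0.10 − 0.20) = 0.143, N = 60, and 1 and 53 degrees of freedom, two-sided power is 82.0% (78.6% under a more conservative noncentrality convention).

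**2. Adjustment at the protocol's assumed 20%.** Residual SD = 0.83 × √(1 − 0.20) = 0.742. At 30 per arm, power for 0.5 becomes 82.4% by exact t, after spending five degrees of freedom on covariates (83.2% normal). The number per arm for 80% power falls from 35 to 28 (normal). This applies the 20% to absolute change.

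**3. Baseline alone, by formula.** The pre-post correlation r is not given, so it is assumed. With equal SDs s before and after, change has variance 2s²(1 − r) and ANCOVA has residual variance s²(1 − r²), a ratio of (1 + r)/2. Taking 0.83 as the SD of change:

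| r (assumed) | Variance ratio | Residual SD | Power, 30 per arm | Implied s = 0.83/√(2(1 − r)) |
|---|---|---|---|---|
| 0.6 | 0.80 | 0.742 | 82.4% | 0.93 |
| 0.8 | 0.90 | 0.787 | 78.4% | 1.31 |
| 0.9 | 0.95 | 0.809 | 76.4% | 1.86 |

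These rows compare ANCOVA with a t-test on absolute change, not with the planned percent-change test.

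**4. Baseline alone, against the planned test.** This was simulated with 2,000 runs per setting, so the Monte Carlo error is about 1 point. Assumptions: mean baseline z 2.3 truncated at the 85th percentile, change SD about 0.83, 30 per arm and four cohorts. The settings below have no cohort effect.

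| Baseline SD | Slope of change on baseline | Percent-change t-test | ANCOVA on baseline |
|---|---|---|---|
| 0.3 | 0 | 72.0% | 72.6% |
| 0.3 | −0.5 | 75.8% | 76.8% |
| 0.5 | −0.5 | 72.6% | 76.3% |
| 0.83 | −0.3 | 72.4% | 77.2% |
| 0.83 | −0.5 | 74.7% | 83.8% |

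The gain runs from about none to about 9 points.

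**5. Cohort.** Adding cohort to the baseline ANCOVA changed power by about +1 to +2.5 points when cohorts held 10% of the residual variance (assumed). When they held none, the effect was nothing or a loss of up to about 1 point.

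**6. Percent change is not baseline adjustment.** The entry limit, the 85th percentile, is z = 1.04; the 99th percentile is z = 2.33. A drop of 0.5 is 0.5/1.04 ≈ 48% at the first and 0.5/2.33 ≈ 21% at the second. Equal absolute benefit therefore counts more than twice as much in a child at the entry limit.

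**The case against.** - **A reader might infer that the regression excludes baseline.** The text does not show this. Sample size allows five control variables and Statistical analysis names three, and the article elsewhere uses the abbreviation before that list where it means for example. Baseline could be one of the other two. What stands is that it is not named.
- **A reader might infer that the primary estimate is biased.** It is not. Under randomisation the unadjusted comparison is valid, its standard error already covers chance baseline imbalance, and regression to the mean affects both arms equally in expectation. Only precision is lost.
- **A reader might infer that the test contradicts a randomisation stratified by cohort.** Blocking is explained by enrolment in cohorts, but stratification is only implied. Cohort is also in the regression already, so this part concerns the primary test alone.
- **Mixed models that use the pre-intervention data are already planned.** This is true and should be credited. They are separate from the test assigned to the primary objective, so they do not repair it. Nor does the regression: it keeps the percent-change outcome, and one of its covariates, percent attendance, arises after randomisation.
- **The gain may be negligible.** This stands as a limit. Strengths and limitations describes the children as nearly all severely obese, which suggests a narrow baseline range. If baseline SD were 0.3 (assumed), baseline could explain at most 0.09/0.689 = 13% of the variance of change, and about 3% at a slope of −0.5.
- **The shortfall from 80% power is a separate matter.** Agreed. It comes from 30 against 35 per arm, not from the missing covariates.

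**Conclusion.** The point holds as one of efficiency and of a poorly chosen scale. The stated primary test uses neither baseline BMI z-score nor cohort, baseline is not named in the supporting regression, and percent change neither adjusts for baseline nor matches the absolute 0.5 difference on which the trial was sized.

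At the protocol's assumed 20% explained variability, adjustment would lift power from about 74.6% to about 82%. That figure covers five controls of which only three are named, so it cannot be credited to baseline. For baseline alone, the gain over the planned test lies between about none and about 9 points. The documents cannot narrow this, because they give neither the pre-post correlation nor the baseline SD. The gain from cohort is small and uncertain. The omission itself is clear from the text; its size is not. The change is worth making because it costs so little.

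**What to change.** Make the primary analysis an ANCOVA of post-intervention BMI z-score on arm and baseline BMI z-score, with cohort as a covariate because enrolment and blocking are by cohort. Report the adjusted mean difference with its confidence interval. Keep the percent-change t-test as a sensitivity analysis, and treat continuous secondary outcomes the same way. The longitudinal mixed models can stay as supporting analyses. Settle the wording before outcomes are compared by arm.

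No new data are needed. The statistical cost is a few degrees of freedom: with four cohorts (assumed), one for baseline and three for cohort, out of 58. The larger cost is that the primary measure moves from percent change to the absolute z-score scale. That should be declared openly as a change of measure, although it is the scale that the sample-size section already uses.
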